#### Human behavior adjusted PE analysis

The primary and secondary analyses for the first-time infection, the overall infection, and the examination of the relationship between the ento- and epi- endpoints will also be carried out by adjusting for the human behavior covariates the cloglog models, including “bednet usage” in the last 24 h (Y or N), “travel outside” (Y or N; an individual-level covariate), and the product application rate in each HH (expected to be close to 100%) if the data are balanced between the Y and N categories on “bednet usage” and “travel outside,” and there is practically/clinically meaningful variation in the product application rate across HHs and clusters.

#### Adjusted HBR analysis

The adjusted HBR at a given time point is calculated as the raw HBR× the proportion of people at the risk of being bitten in each HH. Specifically, in each HH where the HBR data are collected in the hourly interval from 6 pm to 6 am, the number of people indoors, the number of people outdoor, the number of people under bednet indoor, the number of people sleeping outdoor is also collected. The adjusted HBR indoor = raw HBR × number of subjects not under the protection of bednet/ total number of indoor subjects, and the adjusted HBR = raw HBR × number of subjects who sleep/total number of subjects outdoor. The analysis specified for estimating the effects of SR on the raw HBR will be applied to the adjusted HBR.

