#### Entomological collections

Twenty clusters (10 SR, 10 placebo) will be randomly selected to estimate the impact of the SR on entomological measures of malaria transmission. Within each cluster, light trap collections will be conducted monthly in 10 randomly selected HHs to assess the impact of SRs on the density of *Anopheles* mosquitoes indoors. The light traps will be deployed next to a person sleeping under a net and will run from approximately 6 pm to 6 am. The 10 SR and 10 placebo clusters will be randomly selected at the beginning of the study and will remain fixed throughout the study. HHs will be sampled with replacement and therefore will be eligible for repeated sampling throughout the study. HHs enrolled in the cohort study will not be eligible for mosquito sampling.

HLCs will be done indoors and outdoors in 6 intervention and 6 control clusters (the 12 clusters will remain fixed throughout the study) in four houses (randomly selected) in each cluster for the period of 2 nights (total of 48 houses across both arms) once every quarter (3 months) to determine the effect of SR on the host-seeking behavior of mosquitoes. The same clusters and the houses will be sampled each sampling period. SR and placebo clusters will be selected in pairs to reduce the degree of heterogeneity between two arms. Sentinel houses will be chosen so they are balanced as to house design and inhabitants to reduce bias due to mosquito density heterogeneity (i.e., some houses may be more attractive to mosquitoes than others). HHs with children enrolled in the cohort are not eligible for the HLCs. One pair of clusters will be sampled on any given night. Collections will start at 6 pm each night with one person inside and one person outside. The teams will collect for 45 min each hour and then take a 15-min break before starting the next hour of collection. At midnight, a new team will begin collecting and will continue until 6 am. Mosquitoes will be sorted by site, date, and time of collection. All mosquitoes will be identified to species and all female anopheline mosquitoes will be tested for the presence of sporozoites by ELISA and/or PCR. A subset of up to 30 per cluster per sampling period will be dissected for parity.

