##### Effects of SR on entomological endpoints

The endpoints in the entomological analysis will include the HBR (number of anopheline caught during the 12-hr interval overnight), anopheline parity rate, anopheline sporozoite rate, anopheline EIR, and the anopheline indoor density collected by light-trap.

We will report the frequencies and proportions of each mosquito Genus and species (anopheline and non-anophelines) collected using HLC and light trap methods across clusters and treatment arm.

The time profile plots of each aggregated entomological endpoint will be obtained over the baseline and intervention period. An appropriate statistical model for the HBR will be identified after examining the distributional characteristics of the HBR data, which are likely to follow (zero-inflated) Poisson distribution, or (zero-inflated) negative binomial distribution if there is over-dispersion. The covariates in the models will include the fixed effects of intervention, time, cluster population size, number of houses in a cluster, location (inside or outside), location and intervention interaction; and a random effect for cluster. The ratio between SR and placebo in HBR will be estimated. A similar model will be applied to analyze the density of mosquitoes caught by light traps. The ratio between SR and placebo on light trap density will be estimated.

The model for parity rate will be the (zero-inflated) Poisson distribution or a (zero-inflated) negative binomial distribution with the daily porous mosquitos as the outcome and the daily HBR as the offset, and the same set of covariates as those used in the model for analyzing HBR. The model for the sporozoite rate will be similar to the parity rate with the change of outcome variable to daily mosquitos with positive sporozoite. Note, if the data on parity and sporozoite positivity are highly unbalanced (not in terms of the distributions between the treatment arms, but the marginal distribution of the variable itself; e.g., 99% nulliparous or 99% negative sporozoite), then the model might lead to unstable estimates or the model might not even converge. In such cases, only summary statistics will be provided.

Summary statistics will be provided on EIR and the insecticide resistance at baseline and per year during the intervention period by treatment group.

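### The count models named for raw HBR are carried over to adjusted HBR, which is not a count; the SR/placebo ratio survives, but the location-by-intervention standard error does not

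*Protocol article*

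**What the plan says.** In the protocol article, the section on effects of SR on entomological endpoints defines the outcome as "HBR (number of anopheline caught during the 12-hr interval overnight", that is, a whole number per night. On the model it says "An appropriate statistical model for the HBR will be identified after examining the distributional characteristics of the HBR data", and adds that the data are "likely to follow (zero-inflated) Poisson distribution, or (zero-inflated) negative binomial distribution if there is over-dispersion". Covariates include location (indoors or outdoors) and the location-by-intervention interaction, with a random effect for cluster. The quantity to be reported is the SR/placebo ratio in HBR.

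The section on the adjusted HBR analysis says "The adjusted HBR at a given time point is calculated as the raw HBR× the proportion of people at the risk of being bitten". The proportion is worked out household by household. Indoors this means "adjusted HBR indoor = raw HBR × number of subjects not under the protection of bednet/ total number of indoor subjects". The modelling instruction is then one sentence: "The analysis specified for estimating the effects of SR on the raw HBR will be applied to the adjusted HBR". The section does not mention non-integer values, rounding, an offset, quasi-likelihood or a robust variance.

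On the size of the data, the section on entomological collections says "HLCs will be done indoors and outdoors in 6 intervention and 6 control clusters". Each cluster contributes four houses, sampled on two nights every quarter.

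**The concern.** A count times a proportion is generally not an integer, and its variance no longer follows the law of the count it came from. Every family named for raw HBR ties the variance to the mean in a way that holds only for the unscaled count. Carrying the analysis over unchanged therefore misstates the record-level variance.

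At stake are the intervals for any term estimated within clusters. The location-by-intervention interaction is the important one, because it says whether the product acts differently indoors and outdoors once net use is allowed for. If an analyst rounded the values so that count software would accept them, the ratio itself would also be at risk.

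**Working it through.** **Inputs from the protocol.** There are 6 + 6 = 12 landing-catch clusters. Catches per location per cluster over 24 months are 4 houses x 2 nights x 8 quarters = 64, so 12 x 64 = 768 house-nights per location. The protocol gives no power or standard-error figure for HBR, so there is nothing to reproduce.

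**Assumptions (not in the protocol).** Mean nightly catch mu from 1 to 20; share at risk p, mainly 0.2; negative-binomial dispersion k = 1-2; true SR/placebo ratio 0.70.

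**1. Record-level variance, constant p.** For Poisson Y with mean mu:
- true variance Var(pY) = p^2 x mu
- variance assumed by a Poisson model for pY: p x mu
- standard-error ratio = sqrt(p x mu / (p^2 x mu)) = 1/sqrt(p) = 1/sqrt(0.2) = 2.24.

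For negative binomial Y, with m = p x mu, the true variance is p x m + m^2/k, against m + m^2/k assumed. Only the first part is misstated, so the error is smaller.

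**2. Record-level variance, p varying between houses.** Let P be the share at risk among N people, with mean p and Var(P) = p(1-p)/N. For Poisson Y, Var(PY) = mu x E[P^2] + mu^2 x Var(P). Take N = 5 for illustration:
- Var(P) = 0.2 x 0.8 / 5 = 0.032
- E[P^2] = 0.04 + 0.032 = 0.072.

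| mu | true variance | Poisson model (p x mu) | SE ratio |
|---|---|---|---|
| 1 | 0.072 + 0.032 = 0.104 | 0.2 | sqrt(0.2/0.104) = 1.39 |
| 10 | 0.72 + 3.2 = 3.92 | 2 | sqrt(2/3.92) = 0.71 |
| 20 | 1.44 + 12.8 = 14.24 | 4 | sqrt(4/14.24) = 0.53 |

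The sign changes at mu = (0.2 - 0.072)/0.032 = 4, so the direction of the error cannot be known in advance.

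**3. Location-by-intervention term.** This contrast is estimated within clusters, so the record-level error passes straight through. Simulations with 12 clusters and 64 catches per location (p = 0.2) gave these ratios of model SE to true SD:
- Poisson, constant p: 2.18
- Poisson, varying p: 0.70 at mean 10; in a further run with 2-7 people per house, 1.22, 0.79 and 0.44 at means 1, 5 and 20, with 90% interval coverage of 95%, 82% and 54%
- negative binomial: 0.93-0.98 with varying p, 1.55 with constant p.

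**4. SR/placebo ratio.** This contrast is between clusters, and the cluster random effect absorbs the error. As an example take mu = 4, constant p = 0.2 and an assumed cluster SD of 0.47 on the log scale (variance 0.2209):
- true within-cluster variance of a log mean: 1/(64 x 4) = 0.0039
- model's version: 1/(64 x 0.8) = 0.0195
- observed spread of cluster means: 0.2209 + 0.0039 = 0.2248
- fitted cluster variance: about 0.2248 - 0.0195 = 0.2053, so the total stays at 0.2248.

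Simulation agrees. The ratio is unbiased, and SE/SD is 0.78-0.93 on scaled values against 0.79-0.92 on raw counts. A second set of runs gave 0.89-1.03 against 0.88-1.00, with 90% coverage of 0.82-0.90 against 0.84-0.88. Since raw counts show the same pattern, the shortfall below 1 does not come from the scaling.

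**5. If values were rounded.** With p = 0.2, catches of 0-2 round to 0, 3-7 to 1 and 8-12 to 2, so the expected rounded value is close to P(Y>=3) + P(Y>=8). For Poisson catches:
- placebo, mean 2: 0.3233 + 0.0011 = 0.3244
- SR, mean 1.4: 0.1665 + 0.0001 = 0.1666
- ratio 0.1666/0.3244 = 0.51, a 49% apparent reduction.

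The same calculation for negative binomial (k = 1-2) gives 38-41% at mean 2. Across both families it gives 33-34% at mean 4 and about 30-31% at mean 8. In simulation, 0.70 became 0.52-0.64 in three of four settings at mean 2, and 0.68-0.69 at mean 10. With more people at risk the bias can reverse: a constant p = 0.5 at mean 1 gave 0.75.

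**The case against.** The strongest reply is that the protocol fixes no count likelihood. The model is to be chosen after looking at the data, and the families are only what is expected. On that reading the carried-over analysis is a procedure, and the details belong in an analysis plan that is not shown. This stands in part, because a non-count model is not strictly excluded. But the choice is tied to the HBR data, no non-count family is named, and the adjusted HBR section adds no separate choice. The parity model's offset shows a tool already in the protocol for scaled counts, but an offset on the log share is undefined when everybody is under a net.

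Two stronger readings are tempting, and the protocol supports neither. One is that the analysis cannot be run, or that its main SR/placebo interval is invalid. Unrounded values can be fitted, and step 4 shows that ratio and its standard error nearly untouched. The other is that rounding will distort the effect. No passage says values are rounded, so step 5 describes a hazard to close off and not a planned step.

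It is also fair to say that a move to negative binomial under over-dispersion removes much of the interaction error, and that adjusted HBR is not a listed outcome and feeds no stated hypothesis.

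**Conclusion.** The instruction is mis-specified, with limited reach. On unrounded values the SR/placebo ratio is sound and its between-cluster standard error is little changed. The location-by-intervention standard error is unreliable. Under Poisson it ranges from about 2.2 times too large (constant p = 0.2) to about 0.7 times the true value (varying p, mean catch 10). Under negative binomial it is about right when p varies and up to about 1.5 times too large when p is constant.

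Only if values were rounded would the ratio move away from 1: a true 30% reduction would read as about 36-49% at mean catch 2 and p = 0.2 in most settings, with little bias at means of 8-10. If the adjustment were made hour by hour, catches per record would be lower and rounding would matter more.

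All sizes rest on assumed catch rates, k and p. The analysis is supplementary and the primary efficacy result is unaffected, so the point is minor.

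**What to change.** In the adjusted HBR section, replace reuse of the raw-HBR count likelihood with one of two methods, both on unrounded values:

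- a log-link mean model for adjusted HBR, fitted by quasi-likelihood or GEE with cluster-robust standard errors and a small-sample correction for 12 clusters; or
- a 6 v 6 comparison of cluster-level log mean adjusted HBR, with a t interval.

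State that adjusted values are not rounded. In a one-location simulation without cluster effects (Poisson catches, p varying between houses), the log-link model with robust variance gave ratios of 0.697-0.701 against a true 0.70. Its 90% coverage was 0.88-0.91 in all nine settings (means 1, 5, 20; shares 0.2, 0.5, 0.8).

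The cost is one sentence and the loss of a full likelihood in a supplementary analysis.

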#### Per-protocol analysis

If the PP sample set differs from the ITT sample set, the primary analysis on the first-time infection and the secondary analysis on the overall infections will also be performed in the PP sample set.

### Methods in analysis to handle protocol non-adherence and any statistical methods to handle missing data {20c}

Standard Operating Procedures have been developed for all study activities and a Clinical Monitoring Plan has been established among the Sponsor, trial implementing partner, and the project Clinical Research Organization - fhiClinical. FhiClinical will be responsible for managing oversight on protocol adherence through interim monitoring visits during the study period. Departures from the protocol that is not participant-specific will be documented on a Protocol Deviation log developed by MRTC and reported as required, and the site re-educated as necessary. Any participant-specific non-compliances and other protocol deviations will be captured in the protocol deviation Case Report Form developed by MRTC and filed as hard copies. Major protocol deviations will be submitted via email to applicable IRBs and the Sponsor within 24 h of PI becoming aware of them, and followed by a detailed report, within 7 working days.

Significant effort will be made to avoid missing values on the outcome (malaria infection status and visit dates, entomological endpoints). When missing values occur for an outcome for reasons not related to the outcome, reasons for missingness and the missing fraction by treatment arm and cluster will be reported. Per protocol, the subjects are screened actively on their malaria status (the outcome) every 4 weeks.

If a subject misses one or more scheduled visits due to reasons not related to the SR product or the outcome, the subject will have missing values on the outcome that can be regarded as ignorable missingness (MAR or MCAR). If a subject drops out of study due to reasons unrelated to the SR product and/or malaria infection, then the missing observations from the subject can be regarded as ignorable missingness (MAR or MCAR). In both cases, all available data from the subject will be included in the primary and secondary analysis, without employing any specific technique to deal with the data.

Missing baseline covariates (individual-level, HH-level, cluster-level) that are a part of the regression models for the outcome of interest will be imputed using simple hot-deck imputation methods if the missing fraction for the covariate is < 5%> If the missing fraction for a covariable is ≥5%, appropriate multiple imputation approaches will be applied. If a non-ignorable portion of the subjects will have missing values on a covariate (due to missing at random or missing completely at random), that covariate may be excluded in the model.

### Plans to give access to the full protocol, participant level-data and statistical code {31c}

The statistical analysis plan (SAP) and analytic code will be made open access. Data and supporting information will be made available 12 months following completion of data analysis and will remain open access in the public domain.

## Oversight and monitoring

### Composition of the coordinating center and trial steering committee {5d}

UND will serve as the lead organization for this program and will assume the overall responsibility for management, oversight, and administration for the program. The coordinating personnel at UND will include the Lead PI, Scientific Director, Program Manager, Program Coordinator, and Finance Manager. UND will communicate on a day-to-day basis with CRS and MRTC. MRTC and CRS will be responsible for running the cRCT on a day-to-day basis which includes but will not be limited to conducting a baseline survey, deploying SRs, entomological monitoring, and subject follow-up. Representatives from MRTC, CRS, and UND will all serve on the data management team to oversee the development and implementation of data collection, recording, and cleaning.

fhiClinical will provide clinical oversight and monitoring of study processes, which includes but is not limited to checking enrolment, GCP training for study staff, ensuring subjects are properly consented, data are appropriately gathered, data quality, safety events are documented and reported as required, investigational product is managed and distributed per specifications, and study close-out activities occur on a timely basis.

### Composition of the data monitoring committee, its role and reporting structure {21a}

The DSMB reviews safety data about the Mali cRCT on an ongoing basis in order to monitor and rapidly identify any accumulating safety issues from across the program and may provide recommendations about stopping the study for safety reasons. Additionally, the DSMB provides additional credibility to study quality, by reviewing summary reports from PIs during baseline and intervention phases and making recommendations as needed about adjustments for study quality reasons. The DSMB consists of a Chair, Medical Monitor, DSMB statistician, and independent statistician.

Safety data should be reviewed routinely and regularly by the DSMB Medical Monitor. If significant concerns would be raised, he/she can engage with the committee. Summary of AEs, SAEs, and death reports observed during the studies should be reviewed by the entire committee at pre-determined checks (quarterly). This should include a comparison of the rate of AE and SAE in the two study arms and at the individual study site. The DSMB will be notified of any SAEs that are “at least possibly related” to the research study as they are reported to PIs. Unblinded efficacy data will be analyzed according to a pre-defined SAP by an Independent Statistician when pre-defined enrolment targets have been achieved. The role of the DSMB statistician will be to agree to what information will be reviewed (see below) and then review and interpret this information with the other DSMB members, perhaps to request further analysis, for example. The DSMB statistician will contribute input to program PIs as to what subset of the SAP is to be presented at different meetings.

Members generally have no ongoing financial relationship with a trial’s commercial sponsor and will not be involved in the trial conduct in any role other than that of a DSMB member. Prospective members will be asked to disclose their financial relationships with any of the sponsors and/or their competitors. The DSMB reports to the Sponsor, UND. The DSMB charter can be made available upon request to UND.

### Adverse event reporting and harms {22}

The SR product contains transfluthrin, a chemical used in currently available HH mosquito control products such as mosquito coils. Exposure to the product may cause mild eye and skin irritation, however, these effects are typically transient and disappear after time. The product may be harmful if chewed on or swallowed, so HH owners will be advised to keep it away from children. The SR product will be fixed at a position out of the reach of children and will be monitored at replacement to ensure it has not been moved. If a product is found to have been removed from its position in the HH, study staff will discuss with the HH owner to determine why it was removed and if there was any problem that led to its removal. Study staff will also reiterate safety precautions that should be taken in regard to the SR product.

AEs and SAEs of interest will be collected through passive surveillance by CHVs on cohort participants and other HH members receiving the study product. Additionally, AE and SAEs of interest will be solicited from study participants during follow-up visits (every 2 weeks) either in the house or clinic. We will also rely on passive surveillance of the outpatient registers at the local health facilities for reports of AE/SAE. Additionally, we may collect unsolicited reports during compound visits and/or product replacement. Anyone experiencing the SAEs or AEs of interest will be encouraged to seek care at the study clinic where clinical staff will attend to them at no cost.

An AE includes any noxious, pathological, or unintended change in anatomical, physiological, or metabolic functions as indicated by physical signs, symptoms, and/or laboratory detected changes occurring in any phase of the clinical study whether associated with the study intervention or placebo. This definition includes an exacerbation of pre-existing conditions or events, intercurrent illnesses. A SAE is any untoward medical occurrence that results in death, is life-threatening, results in persistent or significant disability/incapacity, requires in-patient hospitalization or prolongation of existing hospitalization, or is a congenital anomaly/birth defect in the offspring of a study subject. In addition, important medical events that may jeopardize the participant or may require intervention to prevent one of the other outcomes listed above will be considered serious.

All SAEs will be recorded on the appropriate SAE case report form (CRF), followed through resolution by a study physician, and reviewed by a study physician.

Symptomatic uncomplicated or severe malaria infection will be coded as AEs as will any other acute illness, throughout the 24 months of the study. Clinical malaria will be recorded in the same fashion as other AEs. In general, uncomplicated malaria will constitute an AE and severe malaria will constitute an SAE. Anticipated day-to-day fluctuations of pre-existing conditions that do not represent a clinically significant exacerbation need not be considered AEs. Discrete episodes of chronic conditions occurring during a study period will be reported as AEs to assess changes in frequency or severity. Pre-existing conditions or signs and/or symptoms (including any that are not recognized at study entry but are recognized during the study period) present in a participant prior to the start of the study will be recorded on the participant’s CRF.

AEs will be documented in terms of a medical diagnosis. When it is not possible to make a specific medical diagnosis, the AE will be documented in terms of signs and/or symptoms observed by the investigator or reported by the subject at each study visit. Any hospitalization will be considered a SAE.

AEs to be recorded as endpoints will be pre-defined based on SCJ. toxicology reports of “probable,” “possible,” “plausible,” and “unlikely.” “Probable”includes sensory irritation (oral and dermal). “Possible”includes nausea/vomiting (oral), skin irritation/rash (dermal), and runny nose (inhalation). “Plausible” includes salivation, and “unlikely” includes eye irritation and headache.

AEs and SAEs will be recorded throughout the study. SAEs and the study reports will also be provided to Mali’s Faculté de Médecine et d’Odonto Stomatologie - Faculté de Pharmacie (FMOS-FAPH) ethical committee as required by their current Standard Operating Procedures. Study teams will record AEs for every 2-week surveillance period at the time of house visit (during active malaria detection) and for the 30-day surveillance period at the time of clinic visits (during passive malaria detection). SAEs will be recorded at the time of death, hospitalization. Assessment of SAE relatedness to intervention will be conducted by the study clinician in-country with confirmation/verification by the DSMB Medical Monitor based on the study clinician SAE report and trends in other SAE datasets.

AEs and SAEs will be reported in future publications. Harms will be coded in accordance with MedDRA at time of safety outcome reporting. Summaries of symptom-based AEs, SAEs, and death reports observed during the studies will be reviewed by the trial DSMB at predetermined checks (quarterly). The AE/SAE will be labeled “Probable,” “Possible,” “Plausible,” or “Unlikely” due to SR. Summary statistics of AEs/SAEs, including mean, minimum, and maximum frequencies and percentages across clusters among enrolled subjects, will be provided by the treatment arm. Statistical comparisons of the AE/SAE rates between the two arms will be conducted upon the completion of the study. Two sets of statistical analyses will be run. One set will compare the proportion of having at least one occurrence in each symptom-based AE/SAE during the whole study between the two arms, and the other will compare the total number of occurrences for each AE/SAE between the two study arms. If the data collected permits meaningful statistical hypothesis testing, p-values from the treatment comparisons will be reported, with multiplicity correction via the FDR approach [21].

